#### Validation of self-reported non-nutritional risk behaviors

As described in our conceptual framework, food insecurity may influence risk factors beyond dietary intake, such as tobacco use and stress. Therefore, we will validate self-report tobacco use with serum cotinine, which is recognized by the Centers for Disease Control and Prevention as the preferred biomarker for tobacco use (89). Additionally, we will use regression to assess variance explained in the stress biomarker CRP values by PSS scores. Results from these validation studies will inform selection of appropriate measures to evaluate the impact of the NOURISH-OK intervention on additional health risk behaviors.

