### Diving downstream: Food insecurity as a potential driver of chronic inflammation among PLWH

At a physiologic, downstream level, additional questions exist for how food insecurity gets “under the skin” to produce pathophysiologic responses associated with insulin resistance. One plausible biological pathway linking upstream forces, food insecurity, and its associated risk behaviors to insulin resistance may be through chronic inflammation. Elevated systemic levels of the inflammatory marker C-reactive protein (CRP) have been linked to food insecurity in the general population (29). Chronic inflammation may be an important contributor to dysglycemia (30), diabetes incidence (31, 32), and other chronic co-morbidities (33) among PLWH, who have higher levels of CRP than the general population (33). Measures of body composition, including body fat and muscle mass, are important biological variable predictors of chronic inflammation (34, 35) and insulin resistance (6, 7, 36, 37). Furthermore, HIV lipodystrophy, body composition changes that are characterized by loss of peripheral fat and deposition of visceral abdominal fat, is also linked to higher fasting insulin levels (38). Central adiposity (independent of BMI) (37) and lipodystrophy (38) in PLWH may directly cause insulin resistance due to accumulation of macrophages in adipose tissue, which secrete proinflammatory mediators (e.g., CRP) that impair glucose uptake into cells (39). Among men with HIV, the residual systematic inflammation that remains after viral suppression may be related to ongoing macrophage activation (40). Among women with HIV, food insecurity has been linked to elevated markers of chronic inflammation, even when controlling for viral suppression and CD4+ T cell count (41).

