** *Downstream Pathology* **	
Chronic inflammation	**High sensitivity C-reactive protein** (MSD - Vplex CRP Kit)
Body composition and malnutrition risk indicators	**Wrist circumference:** Measured in centimeters using Singer tape measure to estimate body frame size (ADAM Medical Encyclopedia) (94) **Grip strength:** Measured using dynamometer (Jamar) as screening indicator for malnutrition (95) **Waist circumference:** Measured in centimeters (Adapted from NHANES 2019-2020 Procedures) (96) **Segmental BIA:** Fat, lean dry mass, and phase angle estimates for truncal, right arm, left arm, right leg, left leg, total body (RJL Systems Quantum V Segmental BIA) (97) **Height and weight:** SECA stadiometer Model #220, SECA Electronic Scale Model #703 **Body mass index:** kg/m^2^
Glucose homeostasis	**Impaired fasting glucose:** Defined as fasting plasma glucose between 100-125 gm/dL (98) **Fasting glucose** (MyBioSource – Glucose ELISA) **Fasting insulin** (MSD - Vplex insulin Kit) **HgbA1c** (A1cNOW^®^ PTS Diagnostics)
Insulin resistance (primary outcome)	**Insulin resistance:** Quantitative Insulin Sensitivity Check Index “QUICKI” = 1/[log(I_0_) + log(G_0_)], where I_0_ is fasting insulin (microunits per milliliter) and G_0_ is fasting glucose (milligrams per decaliter) (99)

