#### Estimating dietary intake measurement error

For dietary intake estimates, we will conduct an internal regression calibration study using the sub-sample of 100 subjects with four additional dietary recalls to estimate and adjust for measurement error in the remaining sample with single-day recalls (114). We will use the methods of triads to combine dietary recall data with dermal carotenoid scores to more precisely estimate true carotenoid and total fruit and vegetable intake (115, 116). Since chronic inflammation and smoking are both independently associated with lower beta-carotene concentrations (116), we will control for these confounders, if needed. Additionally, we will explore whether measurement error varies by food security status using sensitivity analysis to estimate and adjust for measurement error at each food security level. We will estimate variance in SAS using the Restricted Maximum Likelihood Estimation method and variance ratios as the error variance/variance across individuals. The within- (CVw=Sw/mean of each nutrient) and between-individual (CVb = Sb/mean of each nutrient) coefficient of variation (CV) will be estimated using Beaton’s formula (117). The CVw will then be used to estimate the number of 24-hr food recall days needed to estimate accurate dietary intakes among PLWH, and whether the number of recall days differ by food security status (117). Findings will be applied to modify the number of dietary recalls collected to evaluate the impact of the NOURISH-OK intervention (Aim 3).

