In addition to elucidating the various potential mechanisms by which food insecurity shapes health risks, the NOURISH-OK study will support validation of dietary assessment measures in PLWH. These measures include dermal carotenoids as a biomarker for total carotenoid and total fruit/vegetable intake and construct validity of the DII^®^ as a predictor of inflammation in PLWH. Because carotenoids, fruits, and vegetables correlate with other nutrients that comprise the DII^®^ score and inflammatory markers, dermal carotenoids may be a useful non-invasive alternative to intensive dietary collection methods in future PLWH studies, including measures of intake and dietary intervention adherence. Although tested extensively in diverse populations (129, 130), this surrogate biomarker has not been studied among PLWH. The NOURISH-OK sub-study will further address methodologic gaps by exploring whether there are differences in dietary intake measurement error based on food insecurity status. If food security status is found to be related to measurement error, it will be paramount that future research investigating the role of food insecurity on dietary intake incorporate methods to adjust for this error. Furthermore, the sub-study’s oral and gut microbiome analyses will answer important questions about whether food insecurity is associated with distinct microbiome profiles and whether these profiles are attributable to diet and insulin resistance among PLWH. Finally, the NOURISH-OK study addresses additional methodologic gaps in health behavior research by including additional validation studies of other lifestyle behaviors among PLWH beyond diet, including self-reported tobacco (validated with serum cotinine) and perceived stress (validated with CRP).

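### Variance in CRP explained by PSS scores is presented as a validation of perceived stress, but it is at most weak construct evidence and could misguide the choice of stress measure for Aim 3

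*Protocol article*

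**What the plan says.** The Protocol article, section *Validation of self-reported non-nutritional risk behaviors*, describes two checks. Self-reported tobacco use is compared with serum cotinine, which the text supports as "recognized by the Centers for Disease Control and Prevention as the preferred biomarker for tobacco use". For stress, "we will use regression to assess variance explained in the stress biomarker CRP values by PSS scores". The section treats both as validation and gives them a use: "Results from these validation studies will inform selection of appropriate measures to evaluate the impact of the NOURISH-OK intervention on additional health risk behaviors". The section before it, on dietary measurement error, identifies the evaluation of the intervention as Aim 3. The Discussion lists the two checks together as validation studies of lifestyle behaviours, the second being "perceived stress (validated with CRP").

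Other parts of the article give CRP a different role. In Table 2 the only entry for chronic inflammation, under Downstream Pathology, is "High sensitivity C-reactive protein". The PSS-10 sits in the same table under Health Behaviors, as the measure of chronic stress. The introductory section on downstream pathways says: "Measures of body composition, including body fat and muscle mass, are important biological variable predictors of chronic inflammation". It also links CRP to food insecurity, reports higher CRP in people living with HIV, and describes adipose-tissue macrophages as a source.

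**The concern.** A validation against a criterion works when the criterion is a direct or specific trace of what the instrument asks about. Cotinine has that standing for tobacco exposure. CRP does not have it for perceived stress. In this protocol it is the general marker of inflammation, with several named sources other than stress.

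The stress-inflammation relation is also something the study sets out to learn. The Objectives hypothesise that non-nutritional health behaviours raise inflammation, and the introduction names chronic stress among the behavioural risk factors. If that relation is unknown, its strength cannot also say how good the stress scale is.

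What is at stake is the interpretation and its use in Aim 3. A sound scale could look poor because stress has little bearing on CRP in this population. A scale could also look well supported because it shares causes with CRP.

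**Working it through.** **Is there a figure to reproduce?** No. The article gives no expected R-squared, threshold or power for this check. The first step is therefore textual, and the numbers in the second are illustrations under assumed values.

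**Step 1: the roles of the two variables, side by side.**

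| Place in the Protocol article | Role of CRP | Role of stress / PSS |
|---|---|---|
| Validation section | Called a stress biomarker, without citation | Scale to be validated |
| Discussion | What stress is validated with | Scale validated |
| Table 2 | Sole measure of chronic inflammation, under Downstream Pathology | Chronic stress, under Health Behaviors |
| Introduction | Inflammatory marker linked to food insecurity, HIV and adiposity | Behavioural risk factor that food insecurity may worsen |
| Objectives and SEM section | Inflammation as a mediator towards insulin resistance | Among the behaviours thought to raise inflammation |

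The stress-biomarker label appears only in the validation section. The rest of the article treats CRP as non-specific inflammation, and PSS-CRP as an association that the conceptual model implies.

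**Step 2: what the R-squared responds to.** Let rel be the reliability of the PSS and rho the correlation between true stress and CRP. With classical measurement error,

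R² = rel × rho².

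| rho (assumed) | rel = 0.5 | rel = 0.7 | rel = 0.9 | rel = 1.0 |
|---|---|---|---|---|
| 0.0 | 0% | 0% | 0% | 0% |
| 0.1 | 0.5% | 0.7% | 0.9% | 1.0% |
| 0.2 | 2.0% | 2.8% | 3.6% | 4.0% |
| 0.3 | 4.5% | 6.3% | 8.1% | 9.0% |

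Going from a poor scale (0.5) to a perfect one (1.0) doubles R². Going from rho = 0.1 to rho = 0.3 multiplies it by 0.09 / 0.01 = 9. A perfect scale with rho = 0.1 gives 1.0 × 0.01 = 1.0%, and a poor scale with rho = 0.3 gives 0.5 × 0.09 = 4.5%. Because rho is unknown, an observed R² cannot be turned into a statement about rel.

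**Step 3: shared causes alone.** Suppose stress has no effect on CRP, but a common cause (adiposity or food insecurity, say) correlates a with one and b with the other. For a perfect scale the induced correlation is a × b and R² = (a × b)²:

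- a = 0.3, b = 0.2: correlation 0.06, R² = 0.36%
- a = 0.4, b = 0.3: correlation 0.12, R² = 1.44%
- a = 0.5, b = 0.4: correlation 0.20, R² = 4.0%

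At the planned n = 500, the smallest correlation significant at two-sided 5% is tanh(1.96 / √497) = 0.088, or R² of about 0.8%. The second and third cases exceed it. An unadjusted regression could then show a significant PSS-CRP association with no stress effect on CRP at all.

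**The case against.** The strongest defence is that relating a scale to a variable it should predict in theory is ordinary construct validation. The Discussion names that approach for the dietary index, and for stress the validation section speaks of variance explained, keeping the verb validate for tobacco. This stands in part: a PSS-CRP association would be some construct evidence. It does not rescue the plan's wording, because the validation section counts both checks as validation studies and the Discussion pairs stress and CRP with tobacco and cotinine as if they were equivalent.

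Several stronger readings are tempting, and the documents do not support them:

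- **That the plan is circular.** Nothing says the validation result decides whether PSS enters the SEM. Figure 3 is not shown, so the exact stress-to-CRP path cannot be seen. Its presence is a reasonable inference from the Objectives, Table 2 and the SEM section, and no more.
- **That Aim 3 would be misguided.** The results are only said to inform selection. No cut-off and no rule for dropping the PSS is given, so the risk is a possibility.
- **That the regression is unadjusted.** Covariates are not stated, and a condensed article may leave them to the full protocol or SAP. The neighbouring carotenoid analysis does foresee control for confounders if needed. The shared-cause illustration applies only so far as adjustment is absent or incomplete.
- **That the regression should be removed.** As a description of an association it does no harm.

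It is also fair to say that PHQ-9 and GAD-7 measure depression and anxiety and are themselves self-reported, so they are not a criterion for stress either.

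**Conclusion.** The concern holds in a limited form. The article twice presents the variance in CRP explained by PSS scores as validation of perceived stress, while its own account of CRP makes it a non-specific inflammation marker. The R-squared reflects mainly the stress-inflammation relation and shared causes. It is at most weak construct evidence and could misguide the choice of stress measure for the intervention evaluation.

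The size cannot be taken from the documents. Under the assumed values, a perfect scale can give anything from 0% to 9.0%, and shared causes alone give 0.4% to 4.0%. These figures show that R² and scale quality come apart; they do not predict the study's result. The conclusion rests on classical measurement error for the formula and on the article's own description of CRP for the argument.

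This is a secondary analysis. The primary QUICKI analysis, the sample size and the data collection are unaffected.

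**What to change.** 1. Remove the Discussion's statement that stress is validated with CRP, and stop counting the PSS-CRP regression among the validation studies.
2. Keep the PSS-CRP analysis, but report it as a test of an association in the model, adjusted for body composition, tobacco and HIV factors. State the covariates. Body composition could be a shared cause or lie between stress and CRP, so its intended role should be said.
3. Base the choice of the PSS-10 for Aim 3 on internal consistency, factor structure and convergent correlation with PHQ-9 and GAD-7, examined across the four food security levels.

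The PSS-10, PHQ-9, GAD-7, anthropometry, cotinine and HIV history are already in Tables 1 and 2, so no new data are needed. The cost is revised wording and a little more analysis. The limitation to state is that PHQ-9 and GAD-7 are self-reported measures of related constructs, so they supply convergent evidence and not a biomarker criterion.

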#### Final structural equation modeling

Finally, we will test our conceptual model using structural equation modeling, a method that allows simultaneous measurement of the strength and significance of predictor variables *via* direct and indirect pathways on a single outcome established *a priori* by theory (118). The theoretical framework draws from existing conceptual models (16, 119) that position physical and social community environments as risk regulators (119) for household food insecurity and its resulting individual nutritional and non-nutritional risk behaviors (16), which become embodied through pathophysiologic responses (119) (**Figure 1**). Sample size recommendations vary widely for studies that employ structural equation modeling, with lower estimates citing 200 cases for SEM models (118). We have selected a conservative sample size of 500, which exceeds more recent recommendations for up to 460 cases for multi-factor, multi-indicator models (120).

The SEM will simultaneously estimate direct and indirect effects of continuous exposure variables in the directional pathway of food insecurity and insulin resistance (**Figure 3**). Specifically, we will test the influence of upstream and social factors on food insecurity, and whether food utilization skills modify the association between community food access and food security. As an intermediate variable in the SEM, food security status will be used to predict insulin resistance using behavioral and pathophysiologic mediators with AIDS diagnosis as a potential effect modifier. We will use similar methods developed in our past research (121), including quasi-maximum likelihood estimation with Satorra-Bentler correction to measure direct and indirect paths between all variables. We will use Chi-square, Root Mean Square Error of Approximation (RMSEA), and Comparative Fit Index (CFI) to assess model fit. We will conduct invariance testing using AIDS status to compare model differences between those with and without AIDS diagnosis history. We will re-specify the model, if needed, using a theory-informed approach. Analyses will be conducted using R, Version 4.0.2.

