### Study population and eligibility criteria

The target population for the NOURISH-OK study is PLWH who are eligible for Ryan White-funded programs and reside in Oklahoma. An estimated 3,000 PLWH access one or more Ryan White-funded programs annually (49) and represent the study’s known recruitment pool. Nearly half (47%) of these individuals identify as a racial or ethnic minority, including 23.8% Black, 5.8% American Indian, and 10.1% Hispanic (49). An estimated 79.7% are male with most Ryan White clients aged 25-44 (42.7%) and 45-64 years (49.2%) (49). Study eligibility criteria require participants be HIV-positive residents of Oklahoma, financially eligible for Ryan White services (i.e., household income <400% federal poverty level), prescribed antiretroviral therapy (ART) for at least the past 6 months, and ability to provide a 10-hour fasting blood sample. Study exclusion criteria includes receiving treatment for cancer or end-stage renal disease.

A preliminary food needs study among Oklahoma Ryan White clients in 2012 found a high prevalence of very low (47.6%) and low (19.5%) food security in this population (62). To test our theoretical model of food insecurity as a central mediator linking upstream and downstream determinants of insulin resistance, representation at each level of food security status is needed. Therefore, selection criteria will be based on a food security pre-screening using the 10-item US Adult Food Security Survey Measure (63). Enrollment goals are based on food security status to ensure equal representation across four categories of food security: high (n=125), marginal (n=125), low (n=125), and very low (n=125) (**Figure 2**).

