#### Nutrition and vital signs assessment

Trained research assistants will then conduct a nutrition assessment including height, weight, waist circumference, wrist circumference, grip strength, and a segmental bioelectrical impedance analysis test. Additional vital signs will include resting heart rate, blood oxygen level, and blood pressure. Resting heart rate, waist circumference, gender, and age will be used to estimate cardiorespiratory fitness (84, 86). We will collect one 24-hr food recall using the Automated Self-Administered 24-hour (ASA24^®^) Dietary Assessment Tool as our primary measure of dietary intake from all subjects (91). We will additionally measure skin carotenoid concentration using Reflections Spectroscopy (RS) (83). This will serve as a concentration biomarker to adjust for measurement error in estimated carotenoid and total fruit and vegetable intake from the ASA24^®^-generated dietary intake estimates.

We will measure height and weight (without shoes) to calculate body mass index (BMI) using a medical grade stadiometer and scale. We will measure central adiposity using waist circumference adapted from NHANES guidelines (96). To minimize participant discomfort, participants will identify body landmarks for self-measure in front of a mirror with assistance from staff. We will conduct segmental bioelectrical impedance analysis (BIA) using the Quantum V Segmental BIA (RJL Systems). Participants who may be pregnant or who have implanted electronic devices will be excluded from this measure. Participants with metal surgical implants present on one side of the body will complete a one-sided measure using the side of the body without the implant. Segmental body fat readings (right arm, left arm, right leg, left leg, and torso) will be used to further identify body type pattern associated with insulin resistance (97). We will minimize BIA measurement error associated with dehydration by providing 16 oz. of water 30 minutes prior to measurement. Collectively, these measures will be used to estimate nutritional and functional status.

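### As named, the structural equation model's estimator drops incomplete records, and the 8% margin of 500 over the cited 460 carries no stated allowance for that

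*Protocol article*

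**What the plan says.** In the protocol article, under Final structural equation modeling, the estimator is named: "quasi-maximum likelihood estimation with Satorra-Bentler correction". The same section bases the sample size on case-count recommendations from the literature. It says these vary widely, "with lower estimates citing 200 cases for SEM models", and then concludes: "We have selected a conservative sample size of 500, which exceeds more recent recommendations for up to 460 cases for multi-factor, multi-indicator models". It gives no alpha, power, effect size or allowance for incomplete records.

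The model draws on several data sources: a fasting blood sample, one dietary recall, chart review (including AIDS history, which is the effect modifier and the grouping variable for invariance testing) and a 233-item self-administered survey.

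Under Nutrition and vital signs assessment, one measure is withheld from some people by protocol, namely segmental bioimpedance: "Participants who may be pregnant or who have implanted electronic devices will be excluded from this measure". For others it is partial: "Participants with metal surgical implants present on one side of the body will complete a one-sided measure". Table 2 lists bioimpedance under downstream pathology, beside waist circumference, body mass index and grip strength, for which no such exclusion is stated. Figure 3, which holds the model diagram, is not available here, and the text does not say which body-composition variable enters the model.

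**The concern.** The Satorra-Bentler correction rescales the normal-theory test statistic and standard errors using moments computed from complete records. Unless a further step is added, a participant with one missing variable leaves the whole model and contributes to no path.

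Two things are at stake. The first is efficiency: someone with observed insulin sensitivity, food security and diet data would be discarded for a missing survey scale. Selection can also enter if those who drop out differ in ways the model does not capture. The second is the sample-size argument, which sets people enrolled against a recommended number of cases. The two are comparable only if nearly every enrolled record is complete on every model variable, and the article does not say that this is expected.

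**Working it through.** **Inputs from the protocol article.** Enrolment is 4 × 125 = 500 (Study population and eligibility criteria). The case-count recommendations are 200 (lower) and up to 460 (upper), from Final structural equation modeling. No missingness rate is given, so every rate below is an assumption.

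**The plan's own figure.** The 500 cannot be derived from a power formula because none is given. It can only be checked as a comparison: 500 − 460 = 40, and 40/500 = 8.0%.

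**Total listwise loss d.** Complete cases = 500 × (1 − d). Enrolment needed to keep 460 complete = 460/(1 − d), rounded up.

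- d = 2%: 490 complete; 470 needed.
- d = 5%: 475 complete; 485 needed.
- d = 8%: 460 complete; 500 needed.
- d = 10%: 450 complete; 512 needed.
- d = 15%: 425 complete; 542 needed.

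The planned 500 is therefore exactly the enrolment that tolerates an 8% loss.

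**Chance of fewer than 460 complete cases.** This is the binomial probability of 41 or more incomplete records out of 500: about 0.2% at an expected loss of 5%, 17% at 7%, 46% at 8% and 92% at 10%.

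**How small losses add up.** If k variables are each missing at rate m, independently, complete cases = 500 × (1 − m)^k.

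- k = 10, m = 1%: 452.
- k = 15, m = 1%, 2%, 3%: 430, 369, 317.
- k = 20, m = 1%: 409.

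The rate per variable at which 460 is reached is 1 − (460/500)^(1/k): 0.83% for k = 10, 0.55% for k = 15 and 0.42% for k = 20.

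Independence matters a great deal here. If the same people were missing everything, a 1% rate on each of 15 variables would cost only 1% in total, leaving 500 × 0.99 = 495 and not 430.

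**Bioimpedance, if it is in the model.** On its own it would have to be missing in more than 40 people to take the count below 460. If it removed an assumed 1% or 5%, the other variables could lose 1 − 0.92/0.99 = 7.1% or 1 − 0.92/0.95 = 3.2% before 460 was reached.

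**The case against.** The strongest reply has five parts.

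- **Missing data may be handled elsewhere.** An article commonly leaves missing-data handling to the full protocol or analysis plan, and naming Satorra-Bentler does not rule out multiple imputation first. This stands in part. The silence itself is no fault, and a reader who inferred that the estimator forces listwise deletion would go too far. But the article does name an estimator, and its default behaviour is to drop incomplete records.
- **No model input is shown to be missing by design.** This stands. A reader might infer it from the bioimpedance exclusions, but the variable list is in a figure not available here, and waist circumference or body mass index could fill that role. The separate survey session within 5 days is a fallback to a single visit, not planned missingness.
- **460 is not a requirement.** This stands. It is the top of a range that starts at 200, and even the 317 in the working stays above 200.
- **Losses may be small and clustered.** This is plausible. Ability to give a fasting sample is an eligibility criterion, food security is measured at pre-screening, the blood measures come from one draw and the scales from one survey. The independence figures show sensitivity and are not predictions.
- **Complete-case estimates are not biased in general.** This stands. Path coefficients remain consistent when missingness depends only on covariates in a correctly specified model. A reader might infer bias on every path unless data are missing completely at random; that is too strong.

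What survives is a named complete-data estimator, foreseeable incomplete records, and a margin that is not described as covering them.

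**Conclusion.** The point holds as an inexpensive improvement to a stated analysis choice. As written, the model would use only participants complete on every model variable, and the comparison of 500 with 460 uses enrolled and not analysable people. The margin is 40 people, and it disappears once total listwise loss exceeds 8%. Whether that happens depends on rates the article does not give: at 5% total loss it is very unlikely (about 0.2%), and at 10% it is likely (92%).

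It is tempting to conclude that the study is too small for its model. The document does not support that, because 460 is a rule of thumb and not a calculated requirement. Falling below it would weaken the claim that 500 is conservative, and no more. Nor do the bioimpedance exclusions alone establish a shortfall: their frequency is not given and their place in the model is not shown.

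**What to change.** 1. Fit the structural equation model by full-information maximum likelihood with robust (Yuan-Bentler type) standard errors and scaled test statistic, so that partly observed participants contribute. Alternatively, keep the Satorra-Bentler fit and precede it with multiple imputation.
2. Report the complete-case fit as a sensitivity analysis.
3. State the expected analysed number, with an assumed rate of incomplete records, and compare that number with 460. Say whether bioimpedance is a model variable and, if so, how withheld and one-sided measurements enter.

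The cost is a few lines of analysis wording; the first option can be run in the same software. There are two downsides. Both options rely on data being missing at random given the modelled variables. And full-information maximum likelihood alone would not recover a participant whose AIDS status is missing, because that variable defines the groups for invariance testing. That case needs imputation or a check of data completeness at enrolment: where charts are not accessible, the fallback described under Chart review and surveys asks for proof of HIV positivity and recent laboratory results but does not mention an AIDS diagnosis date.
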